## Recording and Reporting AEs and SAEs

All AEs and SAEs occurring from the time of randomisation in the Pilot RCT until follow up is completed (12 months post enrolment) must be reported. Depending on the nature of the event, the reporting procedures below should be followed. Any questions concerning adverse event reporting should be directed to the Chief Investigator or the Study Coordinator (Research Associate) in the first instance.

**Adverse Event (AEs):** All non-serious adverse events (as defined in section 9.1 above and including non-serious adverse reactions) during study participation must be recorded on an adverse event/harms case report form and sent to the Study Coordinator within 2 weeks of the event. Severity of AEs will be graded on a three-point scale (mild, moderate or severe). The Study Coordinator will enter the data onto the study database. In addition, the Study Coordinator will contact the LAC team manager monthly to ensure no adverse events are missed.

Expected AEs include the following:

- Severe drug and alcohol use
- Mental health difficulties
- Self-harm and suicidal ideation

**Serious Adverse Event (SAEs):** All SAEs (as defined in section 9.1 above and including serious adverse reactions) during study participation must be reported to the Chief Investigator within 24 hours of the site becoming aware of the event. The initial report should ideally be made by completing the study SAE form and sending via the fax number listed on page 64 of the protocol. Alternatively, if this is not possible, the initial report may be made by telephone to the number listed on page 64 of the protocol. In the case of incomplete information at the time of initial reporting, all appropriate information should be provided as follow-up as soon as this becomes available. Relationship of the SAE to study procedures will be assessed by the Chief Investigator, as will the expected or unexpected nature of the SAE.

As the study deals with a vulnerable population, expected SAEs include those related to the following which result in hospitalisation:

- Severe drug and alcohol use
- Mental health difficulties
- Self-harm and suicidal ideation

SAEs exclude:

- any pre-planned hospitalisations (e.g. elective surgery) not associated with clinical deterioration
- routine treatment or monitoring of the studied indication, not associated with any deterioration in condition
- elective or scheduled treatment for pre-existing conditions that did not worsen during the study

For each SAE the following information will be collected:

- Full details in medical terms and case description
- Event duration (start and end dates, if applicable)
- Action taken
- Outcome
- Seriousness criteria
- Causality in the opinion of the investigator
- Whether the event is considered expected or unexpected (decision to be made by reference to the expected SAEs listed above **only**).

Any change of condition or other follow-up information should be reported to the Study Coordinator (Research Associate) as soon as it is available, or at least within 24 hours of the information becoming available. Events will be followed up until the event has resolved or a final outcome has been reached.

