## Known Risks

Based on previous experience we do not anticipate any significant harm or consequences to result from the interventions. All relevant risk assessments and responses to risk protocols from the participating services will be adhered to. In terms of social harms, the particular focus of the social intervention is on positive support, using a range of strategies to identify those people in the young person’s social environment that could offer this type of positive support. If the interventions uncover unmet medical or psychological need, onward referral to appropriate services will be initiated.

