# SAFETY REPORTING

## Definitions

| Term | Definition |
| --- | --- |
| Adverse Event (AE) | Any untoward medical occurrence in a participant, including occurrences which are not necessarily caused by or related to the intervention under study. |
| Adverse Reaction (AR) | An untoward or unintended response in a participant which is related to the intervention under study i.e. that a causal relationship between the trial intervention and an AE is at least a reasonable possibility and the relationship cannot be ruled out.  All cases judged by either the reporting medically qualified professional or the Sponsor as having a reasonable suspected causal relationship to the trial intervention qualify as adverse reactions. |
| Serious Adverse Event (SAE) | A serious adverse event is any untoward medical occurrence that:   - Results in death - Is life-threatening* - Requires inpatient hospitalisation or prolongation of existing hospitalisation - Results in persistent or significant disability/incapacity - Other important medical events that jeopardise the participant or require intervention to prevent one of the above consequences   * - life-threatening refers to an event in which the participant was at immediate risk of death at the time of the event; it does not refer to an event which hypothetically might have caused death if it were more severe. |
| Serious Adverse Reaction (SAR) | An adverse event that is both serious and, in the opinion of the reporting Investigator, believed with reasonable probability to be due to the trial intervention, based upon the information provided. |
| Unexpected Serious Adverse Reaction (USAR) | A serious adverse reaction, the nature and severity of which is not consistent with the known information about the intervention under study. |

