## Recording and Reporting USARs

All USARs (serious adverse reactions classified as unexpected, as defined in section 9.1) occurring after each participant’s first session of the intervention until their follow up is completed (12 months post enrolment) will be reported to the NHS REC. The CI will perform this reporting.

The assessment of expectedness will be performed by the CI against the known information for the trial.

USARs must be reported no later than 15 calendar days after the CI has first knowledge of the event. Any relevant follow-up information should be sought and reported as soon as possible after the initial report.

As soon as a site suspects that a SAR may be a USAR they must contact the CI, sponsor representative and the research associate immediately by completing an SAE form, and sending it via the fax number listed on page 64 of the protocol.

The reporting timeframe starts at day 0 when the CI is in receipt of a minimum set of information:

- Sponsor trial reference and trial name (sponsor reference)
- Patient trial number and date of birth
- Name of intervention
- Date of notification of the event
- Medical description of the event
- Date and time of the onset of the event (including event end date if applicable)
- Causality assessment
- Seriousness of the event, particularly if life threatening or fatal
- An identifiable reporter (e.g. Principal Investigator)

All sites are expected to fully cooperate with the CI in order that a full and detailed report can be submitted to the NHS REC within the required timelines.

PIs will be informed of all USARs by the CI.

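### Section 9.2 judges expectedness of serious adverse reactions from a list of population background events, contradicting the USAR definition in 9.1 on which the 15-day ethics report in 9.3 depends

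*Protocol*

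**What the plan says.** All references are to the protocol.

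- **Section 9.2 (Recording and Reporting AEs and SAEs)** covers all SAEs and states that serious adverse reactions are among them. It introduces the list this way: "As the study deals with a vulnerable population, expected SAEs include those related to the following which result in hospitalisation". The three entries are severe drug or alcohol use, "Mental health difficulties" and "Self-harm and suicidal ideation". Among the items recorded for each SAE is its expectedness, a "decision to be made by reference to the expected SAEs listed above"; the next word, in bold, is *only*.
- **Section 9.1 (Definitions)** defines a USAR as a serious adverse reaction "the nature and severity of which is not consistent with the known information about the intervention under study".
- **Section 9.3 (Recording and Reporting USARs)** takes its USARs from 9.1 and requires a report to the ethics committee within 15 calendar days. It adds: "The assessment of expectedness will be performed by the CI against the known information for the trial".
- **Section 9.4 (Responsibilities)** gives the Chief Investigator the task of assigning expectedness to serious adverse reactions by medical judgement.
- **Section 6.3 (Known Risks)** says that "we do not anticipate any significant harm or consequences to result from the interventions".

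**The concern.** A list of events that are common in a population answers one question: would this event be surprising in these young people whatever their treatment? The expectedness of a *reaction* is a different question: is this event, already judged related, in keeping with what is known of the treatment's effects? Section 9.2 applies the answer to the first question to events that raise the second, and the word *only* closes off any other source.

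Expectedness decides how a related serious event is handled. In Appendix 1 a related, unexpected event leads to a USAR notification, while a related, expected event ends at the SAE form. The listed categories are also close to the trial's own subject, substance use and mental health, in participants as young as 12. If the list is applied as written, a related hospitalisation in one of these categories may not reach the ethics committee on the 15-day clock, and site investigators may not receive the USAR notice.

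**Working it through.** No arithmetic decides this point. The check is to take one event through each rule: a participant in an active arm is hospitalised for self-harm after a session, and the event is judged related to the intervention.

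| Step | Under 9.2 | Under 9.1, as cited by 9.3 |
|---|---|---|
| Is the event covered? | Yes, reactions are included among SAEs | Yes, it is a serious adverse reaction |
| Reference for expectedness | The three-item list, *only* | What is known of the intervention |
| Basis of that reference | Vulnerability of the population | Effects of the intervention; 6.3 anticipates no significant harm |
| Does severity count? | Not beyond the requirement that the event led to hospitalisation | Yes, both nature and severity |
| Classification | Expected, because self-harm is listed | Unexpected, because 6.3 describes no such harm |
| Route in Appendix 1 | SAE form | USAR notification |
| 15-day ethics report | Not triggered | Required |
| Notice to site investigators | Not triggered | Required |

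The two columns give opposite classifications of the same event, and the Chief Investigator cannot comply with both. Section 9.4 adds a further difficulty: medical judgement has nothing to decide if a closed list is the sole reference.

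**What is the same under both rules.** Section 9.2 sends every SAE to the Chief Investigator within 24 hours of the site becoming aware of it. Section 9.4 sends it on to the Sponsor within 24 hours. Neither step depends on expectedness.

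**Limits of the list.** It covers only events "expected SAEs include those related to the following which result in hospitalisation". A serious event that meets another seriousness criterion without hospitalisation is outside that wording, so it would not be expected even under 9.2.

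**Exposure.** Section 10.3 plans 50 participants in each of three arms. The two active arms therefore hold 2 × 50 = 100 of 3 × 50 = 150 participants. The protocol gives no rate for the listed hospitalisations and none for the share that would be judged related, so the number of affected reports cannot be estimated.

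**Other oversight.** Section 9.4 has the Trial Oversight Committee review safety data for trends. Section 13 schedules its three meetings at the start of the study and at the end of Phases 1 and 2, so none is scheduled while the randomised phase is running.

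**The case against.** The best defence is that the 15-day rule is in 9.3, not 9.2. Section 9.3 points to the 9.1 definition, has the Chief Investigator assess expectedness, and tells sites to make contact at once if they suspect a USAR. The restrictive wording in 9.2 stands in a list of items to be recorded for each SAE. A Chief Investigator who starts from 9.3 and uses the judgement given in 9.4 would reach the intervention-based definition and report the event. This stands to the extent that a missed report is a risk and not a certainty. It does not remove the conflict, because 9.2 states its rule without exception and includes reactions.

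A second defence is that the trial-level information named in 9.3 can be read to include the list, so that 9.2 and 9.3 agree. That reading is possible. It still leaves 9.1, whose wording concerns the intervention and cannot be met by a list based on the population.

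A reader might go further than the documents allow in three ways:

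- **That related events on the list are never expedited.** Sections 9.3 and 9.4 offer another route, so this does not follow.
- **That every related serious event is a USAR because 6.3 leaves nothing known.** Section 6.3 states what is anticipated from previous experience. It does not say that it is the whole of what is known about the interventions.
- **That the listed events are the harms these therapies would most plausibly cause.** Nothing in the protocol establishes this.

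Appendix 1 is not itself at fault. It routes events that have already been classified and sets no reference of its own.

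**Conclusion.** The contradiction is real. Section 9.2 fixes the expectedness of reactions by a closed list of population events. Section 9.1, which governs the expedited report through 9.3, fixes it by what is known of the intervention, and 9.4 leaves it to medical judgement. For a related hospitalisation in any of the three listed categories, 9.2 yields no 15-day report, whereas 9.1 read with 6.3 yields one.

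The effect is confined to the expedited ethics report and the USAR notice to site investigators, and to listed events that led to hospitalisation. Reporting to the Chief Investigator and the Sponsor is unaffected. The conclusion that such an event would be reportable under 9.1 assumes that 6.3 fairly represents what is known about harm from the interventions. The contradiction itself does not need that assumption, since the references differ in kind. This should be corrected, because 9.2 followed literally defeats the protocol's own USAR definition.

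**What to change.** Reconcile 9.1, 9.2, 9.3 and 9.4 so that a single reference governs the expectedness of serious adverse reactions. The reference consistent with the definition that 9.3 already cites is what is known of the intervention. In practice:

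- **9.2:** remove *only* for events judged related, and say that the three-item list describes SAEs anticipated in this population as background. For serious adverse reactions, refer to 9.1.
- **9.3:** replace the phrase about trial-level information with a reference to the 9.1 definition.
- **9.4:** state that the Chief Investigator's medical judgement on reactions is exercised against that same reference.
- **Appendix 1:** the routes can stay as they are.

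The cost is a wording amendment and possibly a few more expedited reports. Sample size, data collection and analysis are unaffected.

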## Recording and Reporting USARs

All USARs (serious adverse reactions classified as unexpected, as defined in section 9.1) occurring after each participant’s first session of the intervention until their follow up is completed (12 months post enrolment) will be reported to the NHS REC. The CI will perform this reporting.

The assessment of expectedness will be performed by the CI against the known information for the trial.

USARs must be reported no later than 15 calendar days after the CI has first knowledge of the event. Any relevant follow-up information should be sought and reported as soon as possible after the initial report.

As soon as a site suspects that a SAR may be a USAR they must contact the CI, sponsor representative and the research associate immediately by completing an SAE form, and sending it via the fax number listed on page 64 of the protocol.

The reporting timeframe starts at day 0 when the CI is in receipt of a minimum set of information:

- Sponsor trial reference and trial name (sponsor reference)
- Patient trial number and date of birth
- Name of intervention
- Date of notification of the event
- Medical description of the event
- Date and time of the onset of the event (including event end date if applicable)
- Causality assessment
- Seriousness of the event, particularly if life threatening or fatal
- An identifiable reporter (e.g. Principal Investigator)

All sites are expected to fully cooperate with the CI in order that a full and detailed report can be submitted to the NHS REC within the required timelines.

PIs will be informed of all USARs by the CI.

## Responsibilities

***Chief Investigator***

- *Clinical oversight of the safety of trial participants, including an ongoing review of the risk/benefit.*
- *Using medical judgement in assigning seriousness, causality and expectedness of SAEs where it has not been possible to obtain local assessment.*
- *Using medical judgement in assigning expectedness to SARs*
- *Immediate review of all USARs.*
- *Review of specific SAEs and SARs in accordance with the trial risk assessment and protocol.*
- *Checking for AEs and ARs when participants attend for treatment or follow-up*
- *Ensuring that all SAEs and SARs, including USARs, are recorded and reported to the Sponsor within 24 hours of becoming aware of the event and provide further follow-up information as soon as available.*
- *Ensuring that AEs and ARs are recorded and reported to the Sponsor in line with the requirements of the protocol.*
- *Expedited reporting of USARs to the REC within required timelines*
- *Notification to all investigator sites of any USAR that occurs*

***Sponsor***

- *Review of any USARs*

***TOC***

- *Review of safety data collected to date to identify any trends*

## Notification of Deaths

All deaths will be reported to Sponsor irrespective of the cause of death.

## Reporting Urgent Safety Measures

An Urgent Safety Measure (USM) is an action that the Sponsor or an Investigator may take in order to protect the subjects of a trial against any immediate hazard to their health or safety. Upon implementation of an USM by an Investigator, the Sponsor and CI must be notified immediately and details of the USM given.

All members of the research team are responsible for reporting (to the Sponsor or delegated party) if they believe that the implementation of safety measures is required. The following procedure should be followed if the Study Coordinator (Research Associate) becomes aware of information that indicates an immediate change in a trial procedure, or that a temporary halt to a trial may be necessary in order to protect trial participants from any immediate hazard to their health and safety:

The Study Coordinator (Research Associate) should immediately record the details of the incident on the current version of the NCTU incident report form. They should then inform the CI, Sponsor (via their designated representative), and/or other designated individual (such as nominated senior NCTU personnel, who has been delegated the responsibility for decision making with regard to urgent safety measures), with full details of the information they have received relating to the incident.

The individual designated to make a decision about implementing safety measures (CI) will consider whether urgent safety measures are necessary to protect participants against any immediate hazard. If trial participants are at risk, the designated individual should inform the NCTU that urgent safety measures are to be implemented so that proposed actions can be agreed.

Verbal notification, via telephone, should then be provided to the main REC and the outcome of these discussions should be summarised on the NCTU incident report form.

The requirement to initiate an urgent safety measure, and the proposed corrective/preventative action, should be communicated to all sites immediately (i.e. within 24 hours of the decision) with acknowledgment of its receipt and implementation received from each PI.

The implemented urgent safety measures (e.g. amendment to protocol, temporary halt to the trial or premature closure of the trial) must be reported by the CI, on behalf of the Sponsor, in writing to the REC within **three days**.

Arrangements for contacting the individual responsible for decision-making with regard to urgent safety measures during extended breaks (for example Christmas and Easter) should be made, to ensure that appropriate cover is in place.

# STATISTICAL CONSIDERATIONS

## Analysis Population

All analyses will be conducted on an intention to treat basis, with sensitivity analyses used to investigate the impact of removing individuals who did not receive the interventions as allocated.

## Statistical Analyses

As a pilot feasibility trial, the main analyses will be descriptive, in order to inform the design of a future definitive study.

### Analysis of the Primary Outcome Measures

The primary outcomes are pilot feasibility outcomes. We will report the numbers of eligible participants seen over the recruitment period, and the resulting rates of recruitment, compliance with randomisation, and data completion. Non completers will be characterised.

### Analysis of Secondary Outcome Measures

The pilot feasibility trial will also assess performance of potential outcome measures for a definitive trial. We will ascertain data completeness of the instruments and any potential bias in the completion of follow-up data to inform the choice of instruments in a future trial. The majority of the outcome data will be presented in simple descriptive tables presenting percentages, means and standard deviations or 5-number summary (as appropriate), for each arm of the study. This information will be used to inform the design, choice of primary outcome, necessary sample size and approach to the analysis, of the future definitive trial.

## Sample Size Calculation

The pilot feasibility trial will aim to obtain data from a minimum of 35 respondents in each trial arm at 12 month follow-up, to estimate the critical parameters to the necessary degree of precision with a continuous primary outcome, (number of occasions drinking 5+ standard drink units in a single occasion as derived from the TLFB/30).[^69^](#_ENREF_69) Assuming a pessimistic 30% loss to follow up, the sample size to be recruited will be inflated to 50 young people in each of the three arms.

# ECONOMIC EVALUATION

## Overview

The purpose of a definitive economic evaluation is to assess benefits as well as costs to patients and their families/carers, the NHS and personal social services. Within the pilot feasibility study we will develop the tools and assess the pilot feasibility of methods necessary to capture the effects of the intervention on health outcomes and associated direct costs. Specifically, we will develop data collection forms and questionnaires to capture use of hospital, primary care and social services and criminal justice resources as well as participant/family/carer costs during the follow-up period. The forms will be tailored to reflect the needs of the study participants and to ensure that there is no double counting of the use of services. For this part of the health economic analyses, data will not be statistically analysed, but rather summarised descriptively to assess the pilot feasibility of data collection instruments.

The findings from the pilot feasibility trial will then be incorporated in a mathematical decision model to provide preliminary estimates of cost, effectiveness and relative cost-effectiveness and assess the value of information (VoI) for a definitive study. It will be conducted from a societal perspective and estimate outcomes and average resource use and associated costs per participant for each trialled intervention. Results from the VoI analysis will provide additional evidence to make the economic case for funding a definitive trial and to assist in the design of that trial.

